#### MRI

We decided to use DSC perfusion, which is the most popular perfusion imaging technique applied (127), particularly due to its very fast acquisition time (approximately 1 min acquisition time), as well as the use of conventional and widely available MRI sequences (e.g., gradient-echo echo-planar imaging, EPI), and its very good contrast-to-noise ratio compared with other perfusion imaging methods, such as ASL and Dynamic contrast-enhanced (DCE). The DSC technique relies on drop in the T2 signal after passing a gadolinium‐based contrast agent (128).

Indeed, when the contrast agent reaches the vessels, it makes them more paramagnetic, and field inhomogeneities around the vessels are created. Thus, the concentration of the contrast agent may be derived from the loss in the signal intensity–time curve due to susceptibility effects of the contrast agent itself.

DSC perfusion may be obtained by using both gradient-echo and spin-echo sequences, which uses a spin-echo-planar scan. On the gradient-echo sequence, the effect of a contrast agent is stronger compared to the spin-echo signal due to the fact that the former has an additional static dephasing of spins in the same inhomogeneous environment. Different studies demonstrated that sensitivity of gradient-echo DSC is similar for a broad range of vessel sizes while spin-echo DSC is particularly sensitive to capillary-sized vessels (129).

A key role in quantifying CBF by using this technique is played by the so-called arterial input function (AIF), which describes the contrast agent input to the tissue of interest. Due to its fundamental role, many studies in recent years have focused on how and where to measure the AIF (global or regional, inside or outside the artery, manually or automatically), how DSC-MRI quantification may be influenced by AIF determination, what artefacts may be related to it, and the design of automatic processes to measure the AIF (127) In this study, we decided to perform a global, automatic, and outside-artery determination of AIF (127).

One of the main limitations of the DCS perfusion technique relies on the possible extravasation of the contrast agent due to the damage of BBB that may lead to T1 and T2* relaxation effects and, thus, to underestimating or overestimating rCBV, respectively (127). These leakage effects may partially be corrected by using a preload contrast bolus OR leakage correction algorithm.

## Conclusion

In this study, it will be important to identify the exact links between activation of coagulation/complement system and brain hemodynamic changes with cerebral hypoperfusion.

We hypothesized that cerebral hypoperfusion in all forms of MS could be the result of the blood flow deceleration mostly in the venous vessel bed during brain inflammatory-thrombotic processes in the course of relapses. Systemic immune activation during the infections influences innate brain immunity and, consequently, adaptive immune response (79, 80). When recurrent and chronic infections, which manifest systemically with immunothrombosis (13), directly or indirectly involve the CNS, it could lead to acute and chronic neuroinflammation. Constant crosstalks between immune cells and coagulation are seminal for an effective immune response (12). While many efforts have been carried out to better define the function of innate immune cells in order to modulate their potential pathogenetic role in MS with specific therapeutic action (5, 6), the coagulant component of innate immunity, which is well studied in animals, has not been sufficiently evaluated in humans. Our working hypothesis is that relapsing patients could have a pro-coagulant condition that may be correlated with blood flow deceleration and the presence of serological indicators of ongoing infection. Whether or not we found correlations between laboratory and MRI parameters, we may see the difference between the relapsing and the remitting MS patient groups. One could argue that peripheral laboratory parameters measured in this study may not fully reflect nor be specific for pathophysiological events occurring in the CNS. However, we hypothesize and believe that events at the CNS level, particularly in MS, could partially represent or be a result of systemic diseases such as infections.

Even if the activation of the coagulation system linked to innate immunity is a mandatory process following different types of tissue damage, interfering with the coagulation system could represent a new therapeutic target in MS. This approach may lead to improved treatment options (e.g., polytherapy) and the development of new therapeutic perspectives for MS and demyelinating diseases in general, but also for other neurodegenerative conditions. It is already possible to interfere with the coagulation system at various levels of the cascade. Therefore, clinical trials trying to transfer the promising results on EAE to humans are needed.

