**Additional secondary outcomes:**

To assess relative CBF, CBV, and MTT by DSC 3.0-T MRI in relapsing MS patients compared to remitting MS patients.To evaluate number and volume of enhancing lesions in relapsing MS patients compared to remitting MS patients.To evaluate the relationships between laboratory data, demographic/clinical (age, gender, disability and disease duration) features, and MRI perfusion findings in the patients’ groups.

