### Selection of Subjects

Subjects of both genders will be recruited in two centers: the Multiple Sclerosis Center of the Sapienza University of Rome and the Multiple Sclerosis Center of the IRCCS Regina Elena National Cancer Institute. The planned recruitment period will be of three years.

Prior to enrollment, all participants will be screened to check their inclusion and exclusion criteria.

Patient inclusion criteria will be:

Patients diagnosed with relapsing-remitting MS (93)Patients untreated or treated with only immunomodulatory therapy18–60 years old

Patient exclusion criteria will be:

pregnancyco-existing neoplastic, hematologic, thyroid, metabolic, thrombotic, or autoimmune diseasesdrug or alcohol addictedtherapy with immunosuppressive drugs, steroids, or any medication interfering with coagulation

We will evaluate 3 groups of subjects: 30 RRMS patients in relapse (Group I); 30 RRMS patients in remission, i.e., without relapse in the previous 2 months (Group II), and 30 sex- and age-matched healthy controls (Group III).

A relapse or exacerbation or “attack” was defined by the multiple sclerosis guidelines as a manifestation of new or worsened neurological symptoms lasting for more than 24 hours (94). Symptoms should be supported by subjective description and by objective clinical assessment with no other explanation for them. The relapse is separated from the previous “attack” by at least 30 days and usually persists for days or weeks, then slowly improves over weeks or a few months ending with partial or complete recovery, i.e., remission. MRI showed the new and/or active lesions in the majority of patients, and steroid therapy often accelerates the recovery of symptoms.

Relapse needs to be distinguished from a pseudo-exacerbation, which is defined as a temporary worsening of pre-existing symptoms without new MS-related neuroinflammation, thus an MRI does not detect active or new lesions (95). The causes of pseudo-relapses could be different and include infections with or without fever, increased body temperature due to over-exercising, sauna, hot shower/bath or weather, dehydration, hormonal changes during menstruation or severe psychological stress, surgery, trauma, medications, alcohol overuse, and several medical conditions as thyroid or other metabolic disorders. Pseudo-relapses usually last less than 24 hours and resolve after removing their triggering causes with no need for steroid therapy.

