On the other hand, healthy people, potentially research subjects, will have only blood sample collection for the pre-specified laboratory assessment; they will not undergo Gd-enhanced MRIs since it represents, in any case, a reasonable low risk related to the use of contrast. Patients will be seen and assessed for physical disabilities using the Expanded Disability Status Scale (EDSS) (97) and Multiple Sclerosis Functional Composite (MSFC) (98).

Each subject included in the study will remain anonymous for privacy reasons and identified by a progressive numeric code (ID number) (associated with their own name, surname, and date of birth in a separate database) so that all serum/plasma samples and MRI data will be treated and processed blindly. An ad-hoc secure database has been established to collect standardized data from different centers, data storage, and sensitive data protection.

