##### Blood Count Test

The CBC is a routine examination of venous blood collected in tubes with EDTA anticoagulant and performed in our laboratory by automatic DxH 800 analyzer provided by the Beckman Coulter company (Brea, California).

The tool provides fast, reliable, and high-quality results thanks to Automated Intelligent Morphology (AIM) and advanced algorithms, and it avoids cellular interference with Coulter’s principle impedance and multi-angle scatter laser.

It analyzes the number of red blood cells (erythrocytes or RBC), white blood cells (leukocytes or WBC), platelets (thrombocytes), hematocrit (HCT), and hemoglobin (Hb) levels of the leukocyte formula (percentage of different white blood cells: neutrophils, lymphocytes, monocytes, eosinophils, and basophils). It determines the physical characteristics of the red blood cells by means of the following indices: MCV (average corpuscular volume), MCH (average corpuscular hemoglobin content), MCHC (Medium Corpuscular Hemoglobin Concentration), RDW (red blood cell distribution amplitude), and MPV platelets (mean platelet volume).

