#### Statistical Methods

Descriptive statistics will be used to summarize pertinent study information. Correlations between quantitative variables will be assessed with the Pearson r correlation. The associations will be analyzed by the Fisher exact test or Chi Square test for trends. Comparisons between disease subgroups and control group will be carried out for different variables, using either Student’s *t-*test or analysis of variance (ANOVA). If the ANOVA shows a statistical difference between subgroups, a post-hoc analysis with Bonferroni correction for multiple comparisons will be performed. For non-normally distributed data, non-parametric (Mann Whitney-U or Kruskal-Wallis-H) tests will be used. The level of significance is set at p ≤ 0.05 (SPSS version 20.0, SPSS Inc., Chicago, Illinois, USA).

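### The secondary marker-perfusion aim is tied to an unadjusted Pearson r, so a shared dependence on age or sex can distort the correlation within either patient group

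*Protocol article*

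**What the plan says.** The aim is the last of the additional secondary outcomes: "To evaluate the relationships between laboratory data, demographic/clinical (age, gender, disability and disease duration) features, and MRI perfusion findings in the patients’ groups". For this kind of data Statistical Methods names one technique: "Correlations between quantitative variables will be assessed with the Pearson r correlation". The other tests in that section (Fisher, chi-square, t-test, ANOVA with Bonferroni, Mann-Whitney, Kruskal-Wallis) are also given without covariates. Under Selection of Subjects, treatment is the one influence that the authors say they will take into account in the final analysis, and no method is attached.

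The same section admits patients aged 18 to 60 in two groups of 30 (relapse and remission). It states sex and age matching only for the 30 healthy controls, and of them it says "they will not undergo Gd-enhanced MRIs".

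The Conclusion gives the working hypothesis that "relapsing patients could have a pro-coagulant condition that may be correlated with blood flow deceleration", and looks for "it will be important to identify the exact links between activation of coagulation/complement system and brain hemodynamic changes with cerebral hypoperfusion".

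**The concern.** Age and sex are listed beside the laboratory and perfusion data as features to be related to them. Nothing shown holds them constant while marker is related to perfusion. If either one influences both sides, marker and perfusion will correlate even among patients in whom coagulation has no bearing on flow at a given age and sex.

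The matching does not help, because it concerns the one group without perfusion data. Analysing relapse and remission separately does not help either, because the spread of age and the mix of sexes exist inside each group.

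A non-zero crude r is a correct description of the data. The problem arises when it is read as a link between coagulation and hypoperfusion, which is the reading that the Conclusion seeks.

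**Working it through.** **The plan's own figure.** Sample Size Calculation gives a detectable difference of 0.71 SD for C4a with 30 per group, 80% power and 5% significance. A one-way ANOVA on three groups of 30, with one group differing by 0.71 SD, has 80.4% power, and the difference detectable at 80% is 0.706 SD. The figure reproduces for that configuration. It concerns the group comparison of C4a and says nothing about the correlation aim.

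**Inputs for the correlation aim.**
- From the documents: n = 30 per patient group or 60 pooled (controls have no MRI), ages 18 to 60, significance at p ≤ 0.05.
- Assumed: a two-sided test; age-marker correlation a and age-perfusion correlation b of equal size and opposite sign; no direct marker-perfusion link. The documents give no value for a or b, so a range is shown.

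**Formula.** If age is the only common cause, the crude marker-perfusion correlation is r = a × b. By Fisher's z, the chance of reaching p ≤ 0.05 is about P(Z > 1.96 − d) + P(Z < −1.96 − d), with d = atanh(|ab|) × √(n − 3).

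**Example, a = 0.4, b = −0.4, n = 60.** r = −0.16; d = 0.1614 × √57 = 1.22; P(Z > 0.74) is about 0.23 and the other tail is negligible, giving 23%.

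**Simulation** (40,000 runs per case, age uniform on 18 to 60):

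| Size of a and b | Induced r | Crude r, n = 30 | Crude r, n = 60 | Age-partial r, n = 30 / n = 60 |
|---|---|---|---|---|
| 0.2 | −0.04 | 5.7% | 6.1% | 5.2% / 5.0% |
| 0.3 | −0.09 | 7.5% | 10.5% | 5.2% / 5.1% |
| 0.4 | −0.16 | 13.6% | 23.0% | 5.0% / 5.2% |

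At 0.3 and 0.4 with n = 60, almost all rejections are negative (10.1 of 10.5 points and 22.9 of 23.0 points). If a and b had the same sign, the rates would be the same and the induced r would be positive.

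**How strong age must be.** The critical |r| is 0.361 at n = 30 and 0.254 at n = 60. For the induced r alone to equal it, a and b must each be about √0.361 = 0.60 or √0.254 = 0.50. Below that, age raises the error rate but does not make a significant result the expected one.

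**Cost of adjusting.** With three covariates, the most that the main analysis would carry (age, sex, and group if pooled), critical |r| goes from 0.361 to 0.381 at n = 30 and from 0.254 to 0.261 at n = 60. The correlation detectable with 80% power, tanh[(1.96 + 0.84)/√(n − 3 − k)] with k covariates, goes from 0.49 to 0.52 and from 0.35 to 0.36.

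**The case against.** The strongest reply is that this is a condensed article. The covariates for a secondary association aim are often left to the full protocol or analysis plan, and the methods paragraph is evidently not complete, since no test in it could carry out the promised weighing of treatment. That stands as a caution: a fuller document may already adjust. But the article does not merely stay silent. It names Pearson r for quantitative variables and reserves its one promise of allowance for treatment.

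A second reply is that the age mechanism comes from outside. That also stands. No passage gives the size or direction of an age effect on any marker or on perfusion. At 0.2 the inflation is negligible, and within one group of 30 it stays modest up to 0.4.

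A reader might infer several stronger points that the documents do not support:
- **That hematocrit is collected and then ignored.** Complete blood count is a key secondary outcome, and "hematocrit (HCT), and hemoglobin (Hb) levels" are part of it, so hematocrit already belongs to the laboratory data to be related to perfusion. Whether to condition on it is a modelling judgement. The documents do not make it a common cause of marker and flow.
- **That the study stands or falls on this correlation.** The Conclusion itself allows that the patient groups may differ whether or not correlations are found, and the primary outcomes are marker concentrations.
- **That age must push every correlation towards the hypothesis.** The primary markers include protein C, protein S and complement components, and the direction is not shown for them.

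**Conclusion.** The point holds for a secondary aim and for age and sex. The stated method cannot separate a coagulation-perfusion link from a shared dependence on age or sex, and neither the matching nor a split by relapse status removes the problem.

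Under the stated assumptions the false-positive rate for a direct link is about 6%, 10% and 23% at assumed correlations of 0.2, 0.3 and 0.4 with 60 patients, and about 6%, 7.5% and 14% with 30, against about 5% after adjustment. These figures are for age alone as the common cause. The argument for sex is the same, but no separate size was calculated. How large the distortion will be in this study cannot be told from the documents. The reason to act is that the correction uses data already recorded and costs very little.

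**What to change.** In Statistical Methods, for the marker-perfusion analyses, replace the plain Pearson r by a partial correlation, or a linear model of perfusion on marker, adjusted for age and sex. Add relapse or remission group as a term if the two patient groups are pooled. Add hematocrit in a sensitivity analysis only. Report the crude r beside the adjusted result, and base any statement of a coagulation-perfusion link on the adjusted estimate with its confidence interval.

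The cost is a few sentences of wording and two degrees of freedom (three if pooled). No new data are needed, and neither the primary outcomes nor the C4a sample size changes.

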## Ethics Statement

The studies involving human participants were reviewed and approved by Local ethical committee of IRCCS Regina Elena National Cancer Institute, Rome, Italy. The patients/participants provided their written informed consent to participate in this study.

